## Abstract

**Background:**

Cytotoxic chemotherapy combinations and targeted agents represent established treatment concepts in advanced pancreatic neuroendocrine tumors (PNETs). However, response rates, side effects and outcome data strongly vary among these therapeutic approaches. Head-to-head comparisons between chemo- and molecular therapies are missing and secondary resistances frequently occur. The RamuNET trial aims to identify the effectiveness of dual treatment with DTIC and ramucirumab in progressive advanced PNET patients.

**Methods:**

The RamuNET study is an investigator-initiated multicenter prospective single-arm trial to evaluate the efficacy of ramucirumab in combination with dacarbazine (DTIC) over a period of at least 6 months. Patients with progressive well-differentiated and metastatic pancreatic neuroendocrine tumors are eligible. The study aims to include 45 patients over a period of 24 months with a minimum follow-up of 24 months. The primary endpoint is disease control after 6 months. Secondary endpoints include progression-free survival, biochemical response, overall survival, quality of life and toxicity. Based on the hypothesis that 80% of the patients can achieve a disease control after 6 months, the sample size calculation follows an exact binomial single-stage design. H0: p < =p_0_ = 60% versus H1: p > =p_1_ = 80%, alpha = 0.05, beta = 0.1.

**Discussion:**

This study investigates a new therapeutic approach using the combination of cytotoxic and targeted antiangiogenic therapy in advanced PNET. If positive, this trial will be the basis for a randomized two-arm study to investigate the combination of ramucirumab and DTIC against other established therapies in PNET.

**Trial registration:**

EudraCT: 2017–001207-68. Date of registration: 2018.01.03.

## Background

Worldwide, the incidence of neuroendocrine neoplasms (NEN) has increased over the last decades [1–3]. In contrast to metastatic NEN of the small intestine which are associated with median 10-year survival rates of 60–70%, metastatic pancreatic neuroendocrine tumors (PNET) have a significantly poorer outcome [3, 4]. Numerous efforts have been taken to improve the long-term outcome of PNET patients. However, the impact of current systemic therapeutic approaches is only modest. Recently, two treatment modalities with targeted agents have been approved: The mTOR inhibitor everolimus and the antiangiogenic multikinase inhibitor sunitinib. Both have demonstrated significant clinical efficacy in prolonging PFS in patients with pancreatic NET [5, 6].

Angiogenesis is a key hallmark of neuroendocrine tumors (NET). VEGF signaling has been described as major determinant of the high vascularity seen in NET both in preclinical models and in human disease [7]. Intratumoral and circulating VEGF levels have been associated with increased tumor aggressiveness and reduced survival of NET patients. Several preclinical studies and clinical trials have evaluated the impact of antiangiogenic approaches in patients with pancreatic NET [8]. The anti-angiogenic multikinase inhibitor sunitinib has shown significant effects on PFS as single agent. However, development of secondary resistance is almost inevitable. Likewise, chemotherapy with temozolomide or capecitabine in combination with the anti-VEGF antibody bevacizumab showed moderate improvements of progression-free survival (PFS) in pancreatic NET (PNET) in phase II trials, but secondary resistance is common and phase III data are still missing [9, 10].

The anti-VEGFR2 antibody ramucirumab alone or in combination with chemotherapy has shown significant effects as second-line treatment in gastric cancer patients [11, 12]. In contrast, antiangiogenic strategies using bevacizumab targeting VEGF as ligand have failed [13]. Similar to gastric cancer, pancreatic neuroendocrine neoplasms are characterized by high vascularity and a high stromal content containing various cellular components with high VEGFR2 expression such as macrophages and endothelial cells [14]. Based on the different VEGFR2-targeting mode of action of ramucirumab compared to VEGF-targeting bevacizumab, we hypothesized that ramucirumab is particularly effective in neuroendocrine neoplasms. Besides its efficacy as single agent and in combination with taxane-based chemotherapy in gastric cancer [11, 12], ramucirumab has been approved for non-small cell lung cancer [15] and in combination with FOLFIRI (leucovorin, fluorouracil, irinotecan) for treatment of patients with progressive metastatic colorectal cancer [16].

In NEN, streptozocin-based (STZ) chemotherapy is frequently used and recommended in symptomatic patients with high tumor load [17]. The use of the combination of doxorubicin with STZ is limited by potential cumulative cardiotoxicity (maximum doxorubicin dose must be less than 500 mg/m^2^) and has been largely replaced by the use of the combination of 5-fluorouracil (5-FU) with STZ [18].

However, randomized phase III data are lacking and thus most evidence was achieved with recently published large retrospective studies [19–21]. An alternative therapeutic option is the alkylating drug temozolomide (TEM) or its derivative dacarbazine (DTIC). While TEM is routinely combined with capecitabine, thus presenting an attractive orally available doublet [9], DTIC monotherapy was recently reinvigorated, based on a large retrospective evaluation [22]. Here, DTIC at a dose of 650 mg/m^2^ was used. A 4-week schedule and a favourable toxicity profile represent relevant advantages of DTIC.

## Rationale for the trial

VEGF receptor-2 (VEGFR2) is the premier receptor responsible for many of the cancer phenotypes, including modification of blood vessel structure and function, proliferation and migration [7, 23]. The fully human monoclonal antibody ramucirumab specifically and potently inhibits VEGF receptor-2 [24, 25].

Based on this specificity, ramucirumab has potential advantages over most other antiangiogenic drugs such as bevacizumab as it is selective for VEGFR2, whereas bevacizumab by targeting VEGF-A affects VEGFR1, −R2, and the noncatalytic coreceptors neuropilin-1and − 2. Ramucirumab thus leaves the VEGFR1 receptor which functions as decoy receptor unaffected, thereby further enhancing the VEGFR2 inhibitory effect [24, 25]. Preclinical and clinical data indicate a pivotal role of VEGFR2 in promoting tumor vasculature and progression in PNETs and suggest an impact of VEGFR2 on acquired resistance [14, 26–28].

In addition, VEGFR2 is highly expressed on macrophages, rendering them a relevant target of ramucirumab. Inhibition of VEGFR2 on macrophages results in decreased tumor immune infiltration, cytokine and chemokine release, leading to impaired tumor growth and proliferation [29, 30]. Own preclinical data indicate that macrophages are expressed at high levels in human and murine pancreatic neuroendocrine tumor tissues and are predominantly polarized towards a protumoral, proangiogenic M2 phenotype, therefore representing a promising target for therapeutic intervention.

Combination regimens using a DTIC-based chemotherapeutic backbone combined with ramucirumab may inhibit early therapy-induced resistance mechanisms by targeting angiogenesis synergistically through different mechanisms. Several preclinical or clinical reports demonstrated a marked antiangiogenic action of DTIC or its oral derivative temozolomide indicating synergism with antiangiogenic targeted agents [10, 31].

Moreover, the combination of ramucirumab and DTIC has already been demonstrated as feasible and associated with an acceptable safety profile in a randomized phase II trial in patients with malignant melanoma [10, 31]. Furthermore, ramucirumab was studied in patients with pretreated gastric neuroendocrine carcinomas in combination with chemotherapy. The results were promising and demonstrated a benefit of dual therapy as opposed to chemotherapy alone [32].

Based on the unique molecular mode of action of ramucirumab and the synergistic potential of DTIC, the combination therapy with both agents represents a promising strategy for progressive pancreatic neuroendocrine neoplasms.

## Methods

### Study endpoints

#### Primary endpoints

Primary endpoint is the disease-control (DC) at 6 months as assessed by RECIST 1.1 criteria. Disease-control will be calculated from start of study treatment until progressive disease. DC is the most important parameter to assess the efficacy of a novel therapy regimen in the population of patients with PNET who frequently undergo multiple lines of loco-regional and systemic treatments.

If a positive DC signal with the combination of ramucirumab and DTIC is observed in this pilot trial, a subsequent evaluation in a randomized phase II/III trial is justified.

#### Secondary endpoints

Objective tumor response (OR)progression-free survival (PFS)overall survival (OS)toxicitiesbiochemical response (tumor marker chromogranin A (CgA); in cases of functional pancreatic NET: the specific hormone can be evaluatedQoL (EORTC QLQ-C30 questionnaire)

### Study population

Patients with histologically confirmed unresectable metastatic non-functional or functional G1-G2 PNET excluding G3 neuroendocrine carcinomas (NEC) or G3 neuroendocrine tumors (NET), who have progressive disease under treatment with either non-DTIC-based chemotherapy (e.g. 5-FU/ streptozocin, capecitabine), SSA analogues, everolimus, sunitinib or PRRT are eligible for screening and enrollment in the trial. The Investigator will keep a record of all study candidates who were considered for enrollment including screening failures.

#### Inclusion criteria

Histologically confirmed unresectable metastatic non-functional or functional G1-G2 PNET excluding G3 neuroendocrine carcinomas (NEC)Age: 18–75 yearsMeasurable disease (RECIST 1.1)Progressive disease under treatment with either non-DTIC-based chemotherapy (e.g. 5-FU/streptozocin, capecitabine), SSA analogues, everolimus, sunitinib or PRRT. No prior therapy with DTIC is allowed.ECOG 0–1Life expectancy > 12 weeksAdequate renal function (serum creatinine ≤1.5 x ULN, or creatinine clearance (measured via 24-h urine collection) ≥40 mL/minute (if serum creatinine is > 1.5 x ULN, a 24-h urine collection to calculate creatinine clearance must be per-formed). Urinary protein is ≤1+ on dipstick or routine urinalysis (UA; if urine dipstick or routine analysis is ≥2+, a 24-h urine collection for protein must demonstrate < 1000 mg of protein in 24 h to allow participation in this protocol).Adequate hepatic function (total bilirubin ≤1.5 mg/dL (25.65 μmol/L), and aspartate transaminase (AST) and alanine transaminase (ALT) ≤ 3.0 x ULN; or 5.0 x ULN in the setting of liver metastases)Adequate bone marrow function (absolute neutrophil count > 1500/mm^3^, platelets > 100,000/mm^3^, hemoglobin> 9 g/dL)Adequate coagulation function (INR ≤1.5 and PTT ≤ 5 s above the ULN (unless receiving anticoagulation therapy)Pathological condition present that carries a high risk of bleeding (for example, tumor involving major vessels or known varices)The patient, if sexually active, must be postmenopausal, surgically sterile, or using effective contraception (hormonal or barrier methods, Pearl Index < 1)Female patients of childbearing potential must have a negative serum pregnancy test within 7 days prior to first dose of protocol therapyThe patient must be able to understand, consent and sign the written consent form

#### Exclusion criteria

Pregnancy (positive urine or blood pregnancy test) or lactation.Secondary malignancies in patient’s history with the exception of: disease-free period > 5 years before randomization or basalioma of the skin or carcinoma of the cervix after successful therapyAllergy against dacarbacine or ramucirumabCurrent enrolment or participation within the last 4 weeks in a clinical drug trialAny arterial thromboembolic events, including but not limited to myocardial infarction, transient ischemic attack, cerebrovascular accident, or unstable angina, within 6 months prior to first dose of protocol therapyInsufficient liver function: cirrhosis at a level of Child-Pugh B (or worse) or cirrhosis (any degree) and a history of hepatic encephalopathy or clinically meaningful ascites resulting from cirrhosis. Clinically meaningful ascites is defined as ascites from cirrhosis requiring diuretics or paracentesis.Uncontrolled or poorly-controlled hypertension (> 160 mmHg systolic or > 100 mmHg diastolic for > 4 weeks) despite standard medical managementChronic antiplatelet therapy, including aspirin, nonsteroidal anti-inflammatory drugs (NSAIDs, including ibuprofen, naproxen, and others), dipyridamole or clopidogrel, or similar agents. Once-daily aspirin use (maximum dose 325 mg/day) is permittedGrade 3–4 GI bleeding within 3 months prior to first dose of protocol therapy.History of deep vein thrombosis (DVT), pulmonary embolism (PE), or any other significant thromboembolism (venous port or catheter thrombosis or superficial venous thrombosis are not considered “significant”) during the 3 months prior to first dose of protocol therapyUncontrolled severe physical or mental disorders such as: neurological or psychiatric disorders including seizure, advanced dementia, psychosis, active uncontrolled infections or sepsis, HIV, replicative hepatitis B or C infectionPathological condition present that carries a high risk of bleeding (for example, tumor involving major vessels or known varices)History of gastrointestinal perforation/fistula (within 6 months of first dose of protocol therapy) or risk factors for perforation.Major surgery within 28 days prior to first dose of protocol therapy, or minor sur-gery/subcutaneous venous access device placement within 7 days prior to first dose of protocol therapyElective or planned major surgery to be performed during the course of the clinical trial.Serious or nonhealing wound, ulcer, or bone fracture within 28 days prior to first dose of protocol therapy.

### Trial design

RamuNET is a multicenter single-arm pilot study. Patients are recruited in approximately 8 participating centres that are all University hospitals or tertiary referral hospitals in Germany with excellent expertise in the care of patients with neuroendocrine neoplasms. A recruitment of an average of 5 patients with progressive PNET per centre over a period of 12 months seems realistic.

### Conduct of the trial

There is a screening period of 28 days. All required study procedures are listed in Table 1. After study enrollment, therapy continues for 6 months (primary endpoint) or until tumor progression. If patients are stable after month 6, treatment can be continued until progression or toxicity). Patients will be followed-up at least 24 months from the start of the study. Finally, the final data analysis is performed (Fig. 1).

**Table 1 Tab1:**
[figure not shown]
Requirements for the study

^1^every 3 months;

^2^if no imaging has been performed within the last 4 weeks.

^3^to be performed at the beginning of each cycle.

^4^to be followed beyond the 30 days until resolution or stabilization

**Fig. 1 Fig1:**

Study procedure

### Study treatment

Ramucirumab at a dose of 8 mg/kg body weight, is administered i.v. on days 1 and 15 of each 28-day cycle, over a time period of 60 min prior to administration of dacarbazine (DTIC). DTIC is given at a dose of 650 mg/m^2^ body surface area on day 1 and then once every 4 weeks as intravenous infusion over 30 min as previously described [22]. Overall the study treatment includes 6 cycles of the combination therapy (Fig. 2).

**Fig. 2 Fig2:**
[figure not shown]
Therapy schedule and endpoints of the study

### Translational program

This study concept is supported by own preclinical data indicating high amounts of VEGFR2 positive tumor-infiltrating macrophages in PNET tissues as therapeutic targets as well as literature reports from other groups and clinical trials in other tumor entities supporting the combination of anti-VEGFR2 together chemotherapy including DTIC. These data indicate that systemic administration of ramucirumab may overcome therapy resistance by affecting both the tumor cell compartment and also the local and systemic innate immune response, leading to a modulation of tumor-associated macrophages towards an antimetastatic phenotype.

The protocol includes analysis of biopsy specimens as well as resected tumor specimens in case of previous surgeries in the participating patients. The aim of the translational program is to correlate response patterns to ramucirumab with characteristic features in the tumor tissue. All participating centers are requested to send tissue blocks from biopsies or previous surgeries for central translational analyses.

Histopathological analysis of tumor specimens will be performed centrally at the Institute of Pathology, Martin Luther University of Halle, Germany. This includes confirmatory analysis of proliferation rate (Ki-67) and tumor grading as well as VEGFR2 expression in tumor and surrounding stromal cells. In addition, infiltration of macrophages (CD68, CD204, CD163, VEGFR2) and different T cell subpopulations (CD3/CD8: cytotoxic T cells, FoxP3: regulatory T cells) will be assessed to correlate infiltration with tumor-associated macrophages and cytotoxic or regulatory T cells with subsequent response to ramucirumab therapy. In addition, immunohistochemical analyses will be performed for angiogenesis (microvessel density; CD31) and epithelial-mesenchymal transition (EMT, E-cadherin, vimentin). Both angiogenesis and EMT are known to be modulated by tumor-associated macrophages and modulate metastasis formation and might serve as predictors of response to bisphosphonates.

In addition to immunohistochemical analyses on resected tumor specimens, we will examine circulating biomarkers in serum to identify predictors of response to ramucirumab or prognostic parameters as liquid biopsies. Serum and plasma will be used for central analysis of circulating, macrophage-associated cytokines and mediators of angiogenesis (e.g. IL1, IL6, VEGF, Angiopoetin-1 / -2) and correlated to clinical parameters.

### Statistical analyses

This trial is planned as a pilot study to evaluate the efficacy of combination treatment of ramucirumab and dacarbazine. Based on the hypothesis that 80% of the patients can achieve a disease control (DCR = CR, PR and SD) after 6 months. The sample size calculation follows an exact binomial single-stage design [33]. H0: p < =p_0_ = 60% versus H1: p > =p_1_ = 80%, alpha = 0.05, beta = 0.1. 45 patients will be recruited in the participating centers during a period of one year. If the primary endpoint of this pilot trial lies within in the confidence interval, thereby demonstrating clinical efficacy of the combination treatment, the aim is to corroborate these data in a randomized phase II study.

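### The stated success rule, that the endpoint lies within a confidence interval, is not the exact binomial test of 60% that sized the trial

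*Protocol article*

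**What the plan says.** The protocol article, under Statistical analyses, first fixes a design: "The sample size calculation follows an exact binomial single-stage design", with "H0: p < =p_0_ = 60% versus H1: p > =p_1_ = 80%, alpha = 0.05, beta = 0.1" and 45 patients. The planning assumption is given as "Based on the hypothesis that 80% of the patients can achieve a disease control (DCR = CR, PR and SD) after 6 months".

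The last sentence of that section then says what counts as success: "If the primary endpoint of this pilot trial lies within in the confidence interval, thereby demonstrating clinical efficacy of the combination treatment", in which case a randomised phase II study is to follow. It does not say which interval is meant, at what level, or what value has to lie inside it.

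Nothing elsewhere restates the criterion. The abstract repeats the hypotheses and speaks of a follow-on trial if the result is positive. The Primary endpoints section says only "If a positive DC signal with the combination of ramucirumab and DTIC is observed in this pilot trial".

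**The concern.** A test of a rate of at most 60% succeeds when the data rule out 60%, that is, when the whole interval lies above it. A rule under which something lies inside the interval asks whether the data are compatible with a value. That is a different question and can give the opposite answer. The sentence is also the article's only express criterion for having shown efficacy.

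Two things are at stake. First, if the sentence is followed, the alpha of 0.05 and beta of 0.1 in the same paragraph do not describe the decision actually made. Second, the sentence has several readings that give different verdicts on the same count, so the reading could be settled after the count is known. The decision that depends on it is whether to start a randomised trial.

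**Working it through.** **Inputs** (all from Statistical analyses): p0 = 0.60, p1 = 0.80, alpha = 0.05, beta = 0.1, n = 45, exact binomial, single stage. X is the number of patients with disease control at 6 months.

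**Step 1: reproduce the plan's sample size.** Look for the smallest n that has a cut-off r with P(X ≥ r | n, 0.60) ≤ 0.05 and P(X ≥ r | n, 0.80) ≥ 0.90.

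- One-sided 0.05: n = 45, r = 33. P(X ≥ 33 | 45, 0.60) = 0.0446 and P(X ≥ 33 | 45, 0.80) = 0.9005. No smaller n works.
- One-sided 0.025: n = 57, r = 42.

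So 45 is correct, and it corresponds to a one-sided 0.05 test with success at 33 or more of 45 (73.3%).

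**Step 2: put the success sentence into numbers.** Level, method and target value are not stated, so each reading adds assumptions.

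*Reading A: the observed rate lies in its own interval.* This holds for all 46 outcomes (0 to 45 of 45) with Clopper-Pearson, Wilson and Wald intervals. P(success | 0.60) = 1.

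*Reading B: the planned 80% lies in the interval around the observed rate.*

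| Interval (two-sided) | Success at | P(success), p = 0.60 | P(success), p = 0.80 |
|---|---|---|---|
| 95% Clopper-Pearson or Wilson | 31–41 | 0.143 | 0.962 |
| 90% Clopper-Pearson | 31–40 | 0.143 | 0.937 |
| 90% Wilson | 32–40 | 0.084 | 0.910 |
| 95% Wald | 30–40 | 0.225 | 0.951 |
| 90% Wald | 31–39 | 0.143 | 0.885 |

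For 95% Clopper-Pearson, 31/45 gives 0.534 to 0.818, which contains 0.80 but also 0.60. The interval for 42/45 is 0.817 to 0.986, which lies wholly above 0.80, so 42 to 45 of 45 count as failures. P(31 ≤ X ≤ 41) is 0.962 at a true 80%, 0.671 at 90% and 0.187 at 95%, so the chance of success falls as the true rate rises above 80%.

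*Reading C: the observed rate lies in a fixed interval around 36/45 = 80%.* With 95% Clopper-Pearson (0.654 to 0.904), success is at 30 to 40 and P(success | 0.60) = 0.225. Over the same methods and levels the range is 0.084 to 0.225, and the top counts fail again.

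*Reading D: 60% lies in the interval.* This calls failure to reject a success. P(success | 0.60) is 0.91 to 0.97.

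**Step 3: the charitable reading, lower limit above 60%.** The Clopper-Pearson lower limit for x of n is the Beta(x, n − x + 1) quantile at 0.025 (two-sided 95%) or 0.05 (two-sided 90%, i.e. one-sided 95%).

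| Count | Lower limit, two-sided 95% | Lower limit, two-sided 90% |
|---|---|---|
| 32/45 | 0.557 | 0.580 |
| 33/45 | 0.581 | 0.604 |
| 34/45 | 0.605 | 0.628 |

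With the two-sided 95% interval, 34 are needed: P(X ≥ 34 | 0.60) = 0.0216 and P(X ≥ 34 | 0.80) = 0.826. With the two-sided 90% interval, 33 are needed, which is exactly the design in Step 1.

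**Step 4: does 33 carry over to other numbers analysed?** No. P(X ≥ 33 | 47, 0.60) = 0.099, and P(X ≥ 33 | 43, 0.80) = 0.771. The one-sided 95% lower-limit rule adapts: it requires 35 of 47 (P at 0.60 = 0.028) or 32 of 43 (P at 0.60 = 0.035).

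**The case against.** The strongest reply is that the test is already fixed. Hypotheses, alpha, beta, exact method and n are all stated and coherent, and they determine 33 of 45 without the disputed sentence. On this view the sentence is a garbled gloss, probably meant as a lower limit above 60%, and its main clause only states an intention to go on to a further trial after a pilot.

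Much of this stands. The design is sound, and a statistician working from it alone would reach the right cut-off. But the sentence expressly ties its condition to showing efficacy, it disagrees with the test beside it, and nothing else in the article corrects it. The charitable reading does not settle the matter either, because 33 of 45 passes or fails according to the level chosen.

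A reader might also infer more than the document supports:

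- **That the rule has a 14% false-positive rate.** That figure needs 80% as the target and a chosen level and method, none of which is stated. It is one reading within a range of about 8% to 22%.
- **That the plan will discard the best results.** This follows only where 80% must lie in the interval, or the observed rate in one around 80%. At a true 80%, P(X ≥ 42) is only 1.3%, and the article does not discuss true rates of 90% or 95%.
- **That the missing critical count, or alpha not being labelled one-sided, is a fault.** An article may leave the count to the full protocol or analysis plan, which are not shown. The hypotheses are already directional, and 45 reproduces as the smallest n at one-sided 0.05 but not at 0.025.
- **That power is really 82.6%.** That belongs to a rule the article does not state; it only shows why the level matters.

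**Conclusion.** The point holds as a wrongly stated decision rule, not as missing detail. The sample size is right; the success sentence does not match it. Taken literally, the sentence cannot fail. If it means that 80% lies in the interval, the type I error at 60% exceeds 0.05 under every level and method tried (8.4% to 22.5%), and the highest counts are classed as failures. If it means a lower limit above 60%, the verdict at 33 of 45 is undetermined until a level is given.

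The figures assume 45 patients analysed, two-sided intervals at 90% or 95%, and Clopper-Pearson, Wilson or Wald methods. The conclusion that the sentence and the test differ needs none of these assumptions. An analysis plan that is not shown may state the rule correctly; it would then contradict the published sentence, which would still need correcting.

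**What to change.** Replace the success sentence with, for example:

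*H0 is rejected, and a randomised trial is supported, if the lower limit of the one-sided 95% exact interval (two-sided 90% Clopper-Pearson) for the 6-month disease control rate exceeds 60%. With 45 patients analysed this means at least 33 of 45 (exact one-sided alpha 0.0446; power 0.9005 at 80%). If the number analysed differs from 45, the lower-limit rule applies and the cut-off is recomputed.*

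The lower-limit form should be the rule and 33 of 45 its illustration, because a fixed 33 keeps the stated error rates only at n = 45. The change should be made before the primary endpoint is analysed. The cost is this one replacement passage, carried into the analysis plan if that repeats the present wording; no further patients or data are needed.
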